### Fidelity checks

The interrater reliability of interview assessments with the CAPS, PSP and SCI-SR remission tool is accounted for ingroup wise sessions for interrater reliability enhancement and interrater reliability measurements. Interrater reliability measurements will be carried out monthly, by presenting cases to the research assistants for scoring. All assessments that research assistants will perform at T0, T2, T6 and T12 are presented in a written report, to be reviewed by the researchers.

Therapists receive four days of training in each treatment protocol, that is, PE and EMDR. All treatment sessions will be videotaped. A selection will be rated for treatment fidelity. All therapists will be supervised by highly skilled professionals ([name], [name] and [name], respectively) to evaluate, guide and approve the case conceptualizations and treatment interventions. Monthly, four-hour group supervision supports the therapist for the whole duration of the experimental intervention.

Every session the therapist will fill out a self-report questionnaire about the elements and the steps in the treatment protocol. Deviations from the protocol will be reported to the supervisor.

### Therapist ratings

During the whole process of training and treatment, assessments will be carried out of therapists' opinions and expectations regarding the credibility and burden of treatment. As indicated in the Instruments section the T-TAQ is administered, comprising the ITTEQ-TF*,* the CS-TF and the BS-TF. The ITTEQ-TF is integrated into the training and supervision on PE and EMDR and is rated at different levels: before treatment training ('prior'), halfway through training ('theory'), after training ('first practice'), in therapist group supervision session number four ('novice'), at the end of the supervision series ('competent') and at the half year follow up ('expert'). The session versions of both the CS-TF and BS-TF (CS-TSF and BS-TSF) will be used additionally within treatment sessions one and eight.

The TPE-TS is administered to therapists before and after treatment of each participant.

### Analyses

The primary outcome on the PTSD measures will be analyzed using Linear Mixed Models (LMM) with the baseline value as a covariate. LMM will also be used with the secondary outcome measures. Sensitivity and specificity of the screener will be calculated with Receiver Operating Characteristic curves. The predictors will be assessed with (logistic) regression analysis. The moderator and mediator analyses will be calculated with 5,000 bootstraps [124]. The association between working memory and the outcome of therapy is performed by analysis of covariance (ANCOVA’s) and multiple regression analysis. The ESM data will be analyzed by multilevel linear regression modeling using STATA. In case of an effective treatment a cost-effectiveness analysis will be performed. The incremental cost-effectiveness ratios (ICERs) are considered to be a single-point estimate of an underlying continuum. Acceptability curves are produced with bootstrap simulations and confidence intervals. The outcome will be costs in Euro’s per QALY and the costs in Euro’s per day without PTSD gained. If no intervention is effective, which is not expected, a cost-minimization calculation will be done.

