## Objectives

### Primary objective –effects of treatment on PTSD symptoms and safety

In a sample of patients who receive treatment as usual (TAU) for a current diagnosis of psychosis this study examines: a) the efficacy of PE versus waiting list, and of EMDR versus waiting list, on the symptomatology of a comorbid PTSD; and b) the safety of PE versus waiting list and EMDR versus waiting list in the treatment of PTSD.

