### Secondary objectives - effects of treatment on psychopathology and cost effectiveness

Other objectives were to determine the efficacy of PE versus waiting list and of EMDR versus waiting list on the symptomatology of psychosis. In this context the experience sampling method (ESM) [35] will be applied to examine the effects of treatment on temporal associations between intrusions, daily events and activities, and verbal hallucinations, depression,social functioning andpost traumatic cognitions.An economic evaluation will determine the cost effectiveness of the PTSD treatments.

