## Methods/Design

### Design

The T.TIP study is a single blind randomized controlled trial with three arms: PE, EMDR and a waiting list. The three groups are compared at pre-treatment (T0), at post treatment at two months (T2) and at six months (T6), on a set of variables that are linked to the various research questions. Mediator and moderator variables are assessed again at midtreatment (T1). A 12-month treatment intervention follow-up measurement (T12) will give indications whether treatment effects endure. The waiting list condition will receive the treatment of choice after sixmonths (T6).

The assessing research assistants are blind to the participants’ research condition.

The design of this study was approved by the Medical Ethics Committee of the medical centre of the VU University and is registered as N:36649.029.12.

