### Power and sample size calculation

An F-test over three groups with a medium effect-size of treatment compared to waiting list, alpha .05 and power .80 needs 159 participants. Attrition is estimated conservatively to be high at 33%. The needed number of participants is 240. We will use 3 x 80 participants.

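### Cost-effectiveness is analysed only if a treatment proves effective; otherwise a cost-minimization is substituted, with nothing in the protocol to show that effects are equal

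*Protocol article*

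**What the plan says.** The Analyses section of the protocol article sets a two-branch rule. The first branch is "In case of an effective treatment a cost-effectiveness analysis will be performed". The second is "If no intervention is effective, which is not expected, a cost-minimization calculation will be done". For the first branch it names the outcomes, "The outcome will be costs in Euro’s per QALY and the costs in Euro’s per day without PTSD gained", and the treatment of uncertainty: "Acceptability curves are produced with bootstrap simulations and confidence intervals".

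The Secondary objectives section states the economic aim without any condition: "An economic evaluation will determine the cost effectiveness of the PTSD treatments".

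The clinical comparisons are of efficacy. The Primary objective section names "the efficacy of PE versus waiting list, and of EMDR versus waiting list, on the symptomatology of a comorbid PTSD", and the sample size section reads "An F-test over three groups with a medium effect-size of treatment compared to waiting list, alpha .05 and power .80 needs 159 participants". The CAPS is named as the primary outcome measure. No section gives a criterion for calling a treatment effective, an equivalence margin, or a test of equal effect.

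**The concern.** Cost-minimization drops effects from the comparison and ranks the options on cost alone. That is legitimate when the effects are known, or have been shown, to be the same within a margin that matters. Here the trigger is that no intervention was found effective. In a trial designed to detect a difference, that finding says the difference was not demonstrated, not that it is absent.

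Two things are at stake:

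- In the second branch the protocol's economic question is not answered. The reader gets a cost comparison resting on an untested assumption, in exactly the situation where uncertainty about effects is largest.
- The gate is presumably the PTSD symptom result, but the economic outcomes are QALYs (from the EQ-5D) and days without PTSD. An inconclusive CAPS comparison does not settle the QALY difference, so the rule can discard a cost-utility estimate that the trial could have produced.

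**Working it through.** **Inputs from the protocol article**
- Power and sample size calculation: three-group F-test, medium effect, alpha .05, power .80, 159 evaluable; 33% attrition; 240 randomised, 80 per arm.
- Analyses: mixed model with the baseline value as a covariate; no baseline correlation is given.

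**Assumptions**
- Medium effect means f = 0.25.
- Effective means that a treatment-versus-waiting-list contrast is significant at two-sided .05.
- Baseline correlation r = 0 (unadjusted) or r = 0.5.
- Equivalence margins of 0.2, 0.3 and 0.5 SD, since the protocol gives none.

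**Step 1: reproduce the plan's figures.** Power is taken from the noncentral F with 2 and N − 3 degrees of freedom and noncentrality N × f². With N = 159 and f = 0.25, power is 0.805. The smallest N reaching 0.80 is 158, which is 159 with equal arms. Attrition: 159 / 0.67 = 237.3, so 238, against 240 stated. Both figures reproduce. Evaluable per arm: 159 / 3 = 53.

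**Step 2: how often the fallback would be reached although both treatments work.** The two contrasts share the waiting list, so their test statistics correlate at 0.5. Each has mean d × √(n/2) / √(1 − r²). For n = 53, d = 0.5, r = 0 this is 0.5 × √26.5 = 2.57; with r = 0.5 it is 2.57 / 0.866 = 2.97. The probability that both statistics fall inside ±1.96 (by simulation) is:

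| True effect, both arms | 53 per arm, r = 0 | 53 per arm, r = 0.5 | 80 per arm, r = 0 | 80 per arm, r = 0.5 |
|---|---|---|---|---|
| 0.5 SD | 14% | 6% | 4% | 1% |
| 0.3 SD | 51% | 41% | 36% | 25% |

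**Step 3: what a non-significant contrast leaves open.** The half-width of the unadjusted 95% interval is t(0.975; 2n − 2) × √(2/n). At n = 53 this is 0.385 SD, and at n = 80 it is 0.312 SD. A contrast that just misses significance has an estimate of about one half-width, so its upper limit is about 2 × 0.385 = 0.77 SD, or 2 × 0.312 = 0.62 SD. Both exceed 0.5 SD.

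**Step 4: could the trial show equality instead?** With two one-sided tests at .05, a true difference of zero and 80% power, n per arm = 2 × ((1.645 + 1.282) / margin)².

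| Margin | n per arm needed | Power at 53 per arm | Power at 80 per arm |
|---|---|---|---|
| 0.2 SD | 429 | 0 | 0 |
| 0.3 SD | 191 | 0 | 0.20 |
| 0.5 SD | 69 | 0.65 | 0.87 |

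Only a margin as wide as a medium effect is within reach, and that is the size of benefit the trial is built to detect.

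**The case against.** **The criterion is not stated.** The protocol never says that effective means statistically significant, nor on which outcome or at which time. A reader may infer that the plan openly takes non-significance as proof of equality; the text does not go that far, and the full protocol may define the criterion. This stands as a limit on the wording. It does not rescue the rule, because the article states the substitution outright and gives no evidence of equal effect under any reading.

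**The fallback is unlikely at the planned effect.** This is fair. With baseline adjustment, or with fewer losses than the 33% that the protocol itself calls conservative, the figure at 0.5 SD falls to 6% or below, and the authors say they do not expect this branch. The larger figures need a true effect of 0.3 SD, below the planned one.

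**A condition in the methods narrows an objective; it does not contradict it.** This is also fair. The objective and the rule can both stand, but in the second branch the objective is left unanswered.

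Four stronger readings are tempting and are not supported:

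- *The gate inflates the cost-effectiveness ratio.* Selection on a symptom result biases QALYs only as far as the two correlate, and the documents give no such correlation.
- *The cheapest option would be the waiting list.* No cost estimates are given, and the Discussion expects successful treatment to reduce care use.
- *The economic time horizon is wrong.* The Analyses section states none. The Design and Measurements sections already say that the waiting list is treated from T6 and that T12 is for the PE and EMDR groups.
- *The evaluation should compare PE with EMDR at T12.* The objectives name only comparisons with waiting list.

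**Conclusion.** The concern holds. As written, the rule replaces the cost-effectiveness analysis by a comparison of costs alone whenever efficacy is not shown, with no margin or test to support equal effects, and the trial could not show equality at a narrow margin in any case.

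If effective means significant and both treatments truly work, the fallback is reached in about 1 to 14% of trials at 0.5 SD and about 25 to 51% at 0.3 SD. Within each range the figure depends on retention (53 or 80 per arm) and on an assumed baseline correlation of 0 or 0.5. The fault in the logic is the same at any of these values. The consequence is confined to a secondary objective: the primary analysis, sample size and data collection are unaffected. The rule should be changed.

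**What to change.** In the Analyses section, replace the two conditional sentences with a statement along these lines: irrespective of the clinical result, incremental costs, QALYs and PTSD-free days of PE and of EMDR versus waiting list will be estimated over T0 to T6, the period in which the waiting list is untreated, with bootstrap uncertainty and acceptability curves. Delete the cost-minimization fallback.

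The cost is a change of wording. Table 2 already schedules the TiC-P and EQ-5D at T0, T2 and T6, and the bootstrap and acceptability curves are already named. No visits, measures or participants are added. The Trial status section reports that recruitment is under way, so the change should be made now, before outcome results are known.

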## Discussion

This present so called ‘T.TIP trial’ has several strengths that have the potential of making the T.TIP trial a forerunning experiment.

First, it is hypothesized that the T.TIP trial will make it possible to calibrate an efficacious and efficient short screening tool for assessing PTSD in the group of patients with psychosis. Given the fact that PTSD is underdiagnosed in this patient population [19,20], an instrument that quickly, safely and accurately assesses the risk of PTSD may be a significant aid to clinical practice.

The main goal of the study is to treat PTSD in patients with psychosis. The comparison of two trauma-focused treatments to a waiting list condition will provide answers about the effectiveness of these trauma-focused treatments on PTSD symptoms. This is the first controlled study that directly assesses the effectiveness of two guideline-recommended trauma-focused treatments in this severely mentally ill population that is generally excluded from clinical trials [29]. Further, it is a large study, including enough patients to make powerful conclusions. This would be an important contribution to treatment options for people suffering from psychosis and PTSD, as PTSD symptoms negatively influence the level of functioning and quality of life in patients with psychosis [9,10]. Conceivably, reducing these symptoms will be of great personal value to patients with psychosis who suffer from the consequences of exposure to traumatic events.

What is more, the study is aimed at establishing whether these treatments can be applied safely in this patient population. This is important for the implementation of the treatments, given the fact that clinicians are often hesitant to address issues of exposure to traumatic events in this population because they fear deterioration and crisis [23,24]. Interestingly, in this aspect, we applied short-term (eight sessions) ‘basic’ manualized treatment to this population, without any pre-treatment interventions, such as emotion-regulation, skills training, or stress management. Should these standard trauma-focused treatments prove to be safe, this will strengthen their implementation in clinical practice. A strength of the study is also that it is a multi-center trial, which will enhance the internal and external validity of the interventions.

In addition to PTSD-symptoms and safety, we also studied effects of treatments on psychopathology severity, especially psychotic symptoms. By studying several variables during treatment, we will be able to disentangle the complex interactions between traumatic events, PTSD and psychosis [9-13] and identifying mediators, moderators and predictors of treatment outcome. This is important from a theoretical point of view, but also from a clinical perspective. It will provide practical guidelines for diagnosis and treatment of PTSD in the population of patients with psychosis. One limitation is that only patients are included in the intervention part of the present studywho suffer from psychosis and at the same time meet all PTSD criteria according to the DSM-IV-TR. Should the results on tertiary objectives indicate that there are links between the trauma characteristics and the characteristics of psychosis in this particular group, then these results cannot be generalized automatically to the general population of patients with psychosis (with individuals who have no PTSD symptoms or subthreshold PTSD).

Another important part of the study is the measurement of cost-effectiveness. When PTSD and other symptoms of psychopathology decrease as a result of treatment, it can be expected that patients consume less care, and thereby diminish health costs.

## Trial status

Currently screening and recruiting for participants.

## Abbreviations

AE: adverse events; AHRS: Auditory Hallucination Rating Scale; AVH-BAS: Auditory Verbal Hallucinations Basic Assumptions Scale; BDI-II: Beck Depression Inventory - II; BS-TF: Burden Scale-therapist form; BS-TSF: Burden Scale- therapist session form; BQ: Bullying Questionnaire; BS-PF: Burden Scale – Participant Form; CAPS: Clinician Administered Post traumatic stress disorder Scale; CBT: Cognitive Behavior Therapy; CS-TF: Credibility Scale- therapist form; CS-TSF: Credibility Scale- therapist session form; DACOBS: Davos Assessment of Cognitive Biases Scale; DRS: Delusion Rating Scale; FU: follow up; EMDR: eye movement desensitization and reprocessing; ESM: Experience Sampling Method; EQ-5D™: EuroQol - 5 dimensions; GPTS: Green Paranoia Thought Scale; ITEC: Interview for Traumatic Events in Childhood; ITTEQ-TF: The Impact of Training and Therapeutic Experience Questionnaire – therapist form; MCQ-RF: Memory Characteristics Questionnaire – Revised Form (adapted for T.TIP); M.I.N.I.-plus: M.I.N.I. International Neuropsychiatric Interview-Plus; MOS-SSS: Medical Outcome Studies - Social Support Survey; PBIQ: Personal Beliefs about Illness Questionnaire – Revised version; PE: prolonged exposure; PSP: Social Performance Scale; PSS-SR: Posttraumatic Stress Disorder Symptom Scale - Self Report; PSYRATS: Psychotic Symptom Rating Scale; PTCL: Posttraumatic Cognitions Inventory; RA: Research Assistant; RCT: randomized controlled trial; RIR: Random Interval Repetition; SCI-SR: Structured Clinical Interview for Symptoms of Remission for the PANSS; SERS-SF: Self Esteem Rating Scale - Short Form; SUD: Subjective Unit of Distress; TAEQ: T.TIP Adverse Events Questionnaire; TDQ: T.TIP demographic questionnaire; TF-CBT: trauma focused cognitive behavioral therapy; TiC-P: Trimbos/iMTA questionnaire for Costs associated with Psychiatric Illness - short version; TIS-A-1-SF: Tonic Immobility Scale- Adult Form-Part 1-Short Form; T.TIP screening/TSQ: TTIP screening including the Trauma Screening Questionnaire; VAS: Visual Analogue Scale
